### Trial design

PERFORMUS is a multicentre phase 2 trial with a randomized observational-phase design derived from the design described by Feldman et al. [16]. Patients will be followed up for a total of 12 months. All will start with an observational period (no treatment), then will switch to an experimental period, when they will receive sirolimus. The switch time will be randomized, ranging from month 4 to month 8 (Fig. 1). Such a design was preferred to a two-parallel group design because it allows all children to receive treatment at some time point, thus encouraging physician adherence to the protocol and better patient acceptance. As well, it provides greater power as compared with a two-independent group trial.

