### Eligibility criteria

#### Inclusion criteria

Pediatric patients, age 6 to 18 years, with complicated superficial slow-flow VM extending to underlying tissues (subcutaneous tissue, fasciae, muscles and/or bones) and confirmed by MRI will be eligible. The minimum age of 6 years was chosen to avoid repeated MRI under sedation, as is commonly used for children < 6 years old in most French radiologic centres. Any type of slow-flow VMs, belonging or not to a genetic disorder, might be included, except for pure macrocystic lymphatic malformations, for which sclerotherapy is the usual treatment. Therefore, patients with microcystic lymphatic VMs, mixed micro- and macrocystic VMs, venous malformations or combined lymphatic and venous malformations are eligible if the VM is complicated. Complications might be linked to the volume, pain, functional impairment, bleeding and/or seepage.

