Two blinded independent trained readers will qualitatively assess digital photographs. For each patient, readers will be provided photographs at baseline and those at MS and M12 without informative data; they will be asked to identify which photograph was taken at the end of the observational period and which at the end of the sirolimus period. Such a procedure represents a “lady-tasting-tea” procedure [17]. Guidelines will be given to the investigators to perform, with their own camera, a front, a profile and a ¾ photograph of the VM at a 50 cm-distance, with a decimeter placed beside the malformation, the child being standing up or lying. They will be asked to send a copy of the photographs to the Clinical Investigation Center of Tours for further centralized assessment. The photographs will be previously registered with initials of the names, code of the center and inclusion number.

Clinical global improvement will be assessed by an unblinded physician on a 0–10 visual analog scale and will be self-assessed by the patient or proxy (parents) on a 0–10 visual analog scale.

Impact on complications will be self-assessed by the patient or proxy, considering pain and skin complications/symptoms (seepage, bleeding, skin tension, functional impairment) and quality of life by the dermatological quality-of-life scale (DLQI) and DLQI adapted for children (C-DLQI) [18].

Biologic markers of efficacy will include coagulation explorations (platelet count, fibrinogen level, D-dimers, factor V levels), supporting the presence and disappearance of an abnormal intravascular coagulation consumption, and plasma levels of vascular endothelial growth factor (VEGF) and tissue factor. VEGF is a major angiogenic factor that stimulates the proliferation and migration of endothelial cells. Strong expression of VEGF has been found associated with VAs, and a few reports have shown changes in serum levels of VEGF after efficient treatment for VAs and different vascularized cancers [19, 20]. Moreover, Medici et al. demonstrated that sirolimus in vitro inhibits the proliferation of hemangioma endothelial cells by reducing the expression of VEGF [21]. Hence, VEGF could be a useful biologic marker for treatment monitoring. In addition, tissue factor, a 47-kDa glycoprotein that is the physiological trigger of blood coagulation, probably has a key role in modulation of angiogenesis, particularly by regulating VEGF expression [22, 23].

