### Blinding

The trial will be open-label. With the very nature of the design, blinding is artificial in some way. Indeed, everyone knows that the patient begins with an observational period and ends with a period during which they are treated. Moreover, sirolimus requires biologic monitoring to detect AEs and for dose adjustment (by measuring serum level of sirolimus). Blinding would have involved children undergoing numerous useless blood tests and also important logistical constraints because the people managing the sirolimus adjustment would have to be different from care providers. To compensate for the need for an open-label design, the primary outcome data are collected with blinding (i.e., centralized interpretation of MRI images performed by the same radiologist who will be blinded to physical assessment and treatment period).

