### Statistical methods

Considering the primary outcome, relative changes in volume of VMs will be compared by paired *t* test or Wilcoxon signed-rank test if necessary. For secondary outcomes, physician assessment of efficacy, patient self-assessment and biological relative changes will be analyzed by the same approach (i.e., paired *t* test or Wilcoxon signed-rank test). Considering efficacy on digital photographs, assessed by 2 independent trained readers, the “lady-tasting-tea” procedure will be used to test whether readers performed better than expected in identifying the digital photographs taken after the end of the sirolimus period [17]. Regarding AEs, descriptive statistics (percentages) will be estimated. The ancillary study on genetic samples will be descriptive.

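### The blinded photograph test shows that the switch and month-12 pictures can be told apart, not that the malformation improved, so it does not test efficacy

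*Protocol article*

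**What the plan says.** Protocol article, Secondary outcomes: for each patient, "readers will be provided photographs at baseline and those at MS and M12 without informative data". The two readers are "asked to identify which photograph was taken at the end of the observational period and which at the end of the sirolimus period". The article describes this as a lady-tasting-tea procedure.

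Statistical methods introduces the analysis with "Considering efficacy on digital photographs, assessed by 2 independent trained readers" and says the procedure will "test whether readers performed better than expected in identifying the digital photographs taken after the end of the sirolimus period". No chance level, threshold or rule for combining the two readers is given.

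Trial design fixes the sequence: "All will start with an observational period (no treatment), then will switch to an experimental period, when they will receive sirolimus". Only the length of the first period is random: "The switch time will be randomized, ranging from month 4 to month 8". Blinding, in explaining the open-label design, adds that "everyone knows that the patient begins with an observational period and ends with a period during which they are treated".

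**The concern.** An identification test takes its chance level from the fact that the attribute to be identified was assigned at random. Here it was not. No patient can be on sirolimus at the switch visit and under observation at month 12. A score of 50% is therefore the right reference for the hypothesis that the two pictures cannot be ordered. It is not the right reference for the hypothesis that sirolimus has no effect.

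The readers are also never asked which lesion looks better. A reader who is right because the lesion grew, because the child grew, or because a side effect is visible scores the same as one who is right because the lesion shrank. The article nevertheless presents the result as efficacy.

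The photographs matter because the other clinical efficacy measures are an unblinded physician scale and self- or proxy-assessments in an open-label trial. The Discussion gives the clinical secondary outcomes high importance.

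**Working it through.** **1. Is the question the same as asking which picture is later?** The possible switch months are 4, 5, 6, 7 and 8, and the last picture is at month 12. The gap from the switch picture to the last picture is 12 − 4 = 8 months down to 12 − 8 = 4 months. It is positive in every patient, and the treated picture is always the second one. The two questions therefore have the same correct answer for all patients, and randomising the switch month does not change this.

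**2. Which cues other than benefit are available?**
- Eligibility is "Pediatric patients, age 6 to 18 years", so the children are growing.
- The baseline picture is supplied, so distance from baseline can be judged.
- Background and rationale describes an untreated course that gets worse.
- Investigators use their own cameras.
- The Safety section lists rash among the frequent adverse events.

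Removing labels does not remove these cues. Lesion size against the ruler is not counted here, because it is partly the efficacy signal itself.

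**3. The plan's own figure.** The article gives no figure for the photograph test. The 50 patients come from the primary outcome, and that calculation reproduces. An effect size of 0.4 needs 99 per arm (198, against 200 stated). The paired equivalent is 200 × (1 − 0.5)/2 = 50, with 80.7% power by the normal approximation.

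**4. Threshold.** With n = 50, one reader and reference 0.5, the exact binomial gives:
- P(X ≥ 32) = 0.0325, two-sided p = 2 × 0.0325 = 0.065
- P(X ≥ 33) = 0.0164, two-sided p = 2 × 0.0164 = 0.033

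The only error rate in the article is two-sided 5%, for the primary outcome. On that convention 33 correct are needed.

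**5. No drug effect, time cues present.** Suppose a share f of pairs can be ordered from time cues and the rest are guessed. Then P(correct) = f + (1 − f)/2 = 0.5 + f/2.

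| f (assumed) | P(correct) | P(X ≥ 33) |
|---|---|---|
| 10% | 0.55 | 7.7% |
| 20% | 0.60 | 23.7% |
| 30% | 0.65 | 50.6% |
| 40% | 0.70 | 78.2% |

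With a one-sided 5% test (32 or more) the same shares give 12.7%, 33.6%, 62.2% and 85.9%.

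**6. No drug effect, readers pick the better-looking lesion.** If a share f of lesions is visibly worse at month 12 and the rest are guessed, P(correct) = 0.5 − f/2. With f = 20% this is 0.40. The chance of 33 or more correct is then 0.02%, and the chance of 17 or fewer is 23.7%. The bias is reversed.

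**The case against.** - **The task asks for the period, not the date.** This is true. It becomes a question of order only because the sequence is fixed. The remark in Blinding that everyone knows the sequence explains the open-label design and does not say what the readers are told. But if readers do not know the order, a correct answer still carries no direction of benefit.
- **Time cues are limited.** The pictures are of the malformation at a set distance, and identifying data are already removed. This reduces the cues, perhaps substantially, but does not exclude them.
- **A reader might infer that the test is biased towards a positive result.** The documents do not support that. They describe natural worsening, which pushes the score below 50% for readers who label the better lesion as treated. Neither direction can be presumed.
- **A reader might take the percentages as the expected false-positive rate.** They are not. The documents give no cue share, and the figures are for one reader. The rule for two readers is not stated and may be left to the analysis plan; requiring both to succeed would lower the rate.
- **A reader might infer that the trial lacks any blinded, directional evidence.** It does not. The primary outcome is MRI volume read by a blinded radiologist, and direction is also captured by the physician and patient scales and quality of life.

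What stands is the logical point: success in this test is not evidence of improvement.

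**Conclusion.** The point holds in a limited form. Identifying the end-of-sirolimus picture is equivalent to identifying the later picture, so a better-than-chance score shows only that the two pictures differ recognisably. It is not a valid test of efficacy, in either direction. This follows from the fixed sequence and the wording of the question, and needs no assumption about cues.

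The size of the distortion cannot be derived from the documents. The range of about 8% to 78% rests on assumed cue shares of 10% to 40%, independent pairs, one reader and a two-sided 5% convention borrowed from the primary outcome. The consequence is confined to one secondary outcome. It should be corrected, but it does not threaten the primary analysis.

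**What to change.** Keep the photographs and the readers and change the question. Show the switch and month-12 pictures in random, unlabelled order beside the baseline picture, and ask in which one the malformation is less severe, allowing ties. Test the preference for month 12 against 50%, report the number of ties, and tabulate the preference by randomised switch month.

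State the limits with the result. The answer now has a direction, but it is still confounded with time because the order is fixed. It is conservative if lesions naturally worsen, a drug that only slows worsening may not show, and spontaneous improvement would count in favour of sirolimus. The table by switch month is descriptive: 50/5 = 10 patients per month on average, and time since the switch equals time on treatment, so it cannot separate the two.

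If the present identification question is kept, limit its conclusion to the statement that the pictures can be told apart.

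The cost is a revised reader form and one line of analysis, both settled before the photographs are read. Ties will reduce the number of informative pairs.

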#### Safety

The adverse events (AEs) will be self-declared, through open ended questions which will secondarily be coded. Patients will be questioned about AEs by the investigators, who will particularly check the most frequently AEs reported with sirolimus, i.e. stomatitis, digestive symptoms (nausea, diarrhea), asthenia, cutaneous rash, and infections of mild severity. Lab results are planned before starting sirolimus, then systematically one month after sirolimus is started, then every 2 months until the end of the study (Table 1). Lab results will include complete blood count - the most frequent biological AEs are microcytosis, whose mechanism is not totally elucidated, moderate anemia and decrease in lymphocyte counts -, ionogram, blood lipids, glycemia, and liver and kidney lab tests.

#### Ancillary study

With the organic collection (including blood and skin samples), we will perform genetic analysis of genes involved in vasculogenesis (currently *TIE2* and *PIK3CA*, involved in the mTOR pathway) to allow for a phenotype–genotype association analysis of those VMs [5, 6, 24].

### Participant timeline

Duration of participation will be 12 months for each patient. The time schedule of enrolment and visits is in Table 1.

### Sample size

Because each patient is his/her own control, the randomized observational-phase design is, as a cross-over design, much more powerful than a two-parallel group design. To our knowledge, we have no published data considering both our primary outcome and the target population. We plan to recruit 50 patients. Considering a correlation of 0.5 between the outcomes assessed under the observational and sirolimus period, this sample size will provide the same power as a 200-sample size two-parallel group randomized trial (i.e., 80% power to detect a 0.4 effect size, with a two-sided Type I error of 5%).

### Recruitment

The recruitment of children with these malformations is allowed by the fact that all investigators take part in multidisciplinary consultations dedicated to VAs, including at least dermatologists or other physicians, radiologists, and surgeons. Some of them belong to the French network for research on pediatric dermatology (Groupe de Recherche de la Société Française de Dermatologie Pédiatrique).

## Methods: assignment of interventions

### Allocation

#### Sequence generation and allocation concealment mechanism

Randomization will be handled by a biostatistician not involved in patient recruitment or in their management. We will use a discrete uniform-probability distribution, considering five possible values (i.e., months 4, 5, 6, 7 and 8). Therefore, a randomization sequence with blocks will be generated. No stratification will be considered.

#### Implementation

The allocating sequence will be implemented by means of an electronic Case Report Form (e-CRF): once a patient is included, the physician in charge of this patient will be informed of the treatment switch date.

### Blinding

The trial will be open-label. With the very nature of the design, blinding is artificial in some way. Indeed, everyone knows that the patient begins with an observational period and ends with a period during which they are treated. Moreover, sirolimus requires biologic monitoring to detect AEs and for dose adjustment (by measuring serum level of sirolimus). Blinding would have involved children undergoing numerous useless blood tests and also important logistical constraints because the people managing the sirolimus adjustment would have to be different from care providers. To compensate for the need for an open-label design, the primary outcome data are collected with blinding (i.e., centralized interpretation of MRI images performed by the same radiologist who will be blinded to physical assessment and treatment period).

## Methods: data collection, management, and analysis

### Data collection methods

Table 1 shows data collection according to inclusion and follow-up visits.

### Data management

An e-CRF will be developed by using Ennov Clinical© software. The e-CRF will be managed in agreement with INSERM CIC 1415 Standardized Operating Procedures (SOP). Data from investigating centres will be entered by using a secure web site monitored by clinical research associates, and queries will be edited by data managers, in agreement with an a priori-specified data-management plan. Blinded review will be performed before locking the database. The database will be locked in agreement with INSERM CIC 1415 SOPs and data will be extracted in a SAS format or other, according to statistical requirements. Raw data will be stored in a XML format.

### Statistical methods

Considering the primary outcome, relative changes in volume of VMs will be compared by paired *t* test or Wilcoxon signed-rank test if necessary. For secondary outcomes, physician assessment of efficacy, patient self-assessment and biological relative changes will be analyzed by the same approach (i.e., paired *t* test or Wilcoxon signed-rank test). Considering efficacy on digital photographs, assessed by 2 independent trained readers, the “lady-tasting-tea” procedure will be used to test whether readers performed better than expected in identifying the digital photographs taken after the end of the sirolimus period [17]. Regarding AEs, descriptive statistics (percentages) will be estimated. The ancillary study on genetic samples will be descriptive.

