### Secondary outcomes

Secondary outcomes are clinical and biological assessments of the efficacy of sirolimus as well as safety.

Clinical efficacy will be assessed by different endpoints (Table 1).

**Table 1 Tab1:** Schedule of study interventions, outcome data collection and follow-up visits

	Screening	Inclusion	Switch (start sirolimus)	Switch + M1 ± 15 days	Follow-up during sirolimus treatment: every 2 months ±15 days	End of study
	J-30/J0*	J0	Between month 4 and 8**	Between month 5 and 9**	Between month 7 and 11**	Month 12***
Information	x	x				
Inclusion/exclusion criteria	x	x	x	x	x	
Medical history and demographics	x	x				
Consent		x				
Randomization		x				
MRI	x^1^		x			x
Physical examination		x	x	x	x	x
General laboratory tests		x^2^	x^3^	x^4^	x^4^	
Coagulation markers, serum VEGF, tissue factor		x		x	x	x
Serum level of sirolimus adjustments^5^				x	x	
Blood and skin samples for genetic analysis and collection (ancillary study)		x				
Photographs		x	x			x
Self-assessment for patients and proxy by visual analog scale			x	x	x	x
Dermatological quality of life scale		x	x	x	x	x
Adverse events/serious adverse events^6^				x	x	x

*possibly by call phone

**depending on the date of the treatment switch from observational to treatment stage

***sirolimus might be maintained at the discretion of investigators after the protocol is finished

^1^included in routine care

^2^complete blood count, ionogram, creatinine, urea, liver enzymes (gamma-GT, SGOT, SGPT), cholesterol, triglycerides, glucose, infection with HIV and hepatitis B and C, serum β-hCG or urine pregnancy test for women of childbearing age

^3^complete blood count, ionogram, creatinine, urea, liver enzymes, cholesterol, triglycerides, glucose, urinary pregnancy test on women of childbearing age

^4^every month during sirolimus: complete blood count, ionogram, creatinine, urea, liver enzymes, cholesterol, triglycerides, glucose

^5^performed after 15 days of sirolimus and then once a month

^6^adverse events will be recorded from when the informed consent form is signed

*VEGF* vascular endothelial growth factor

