## Discussion

A randomized trial on sirolimus in VMs was needed, but we had to overcome several difficulties to design such a study: the population is too rare to allow for a parallel-group trial; we have no gold standard for comparing sirolimus; and a placebo group allowing for blinding is not acceptable in this pediatric population because biological samples are required for sirolimus monitoring.

The “randomized observational-phase design” is adapted from the “randomized-placebo phase design” published by Feldman, developed to suit rare conditions for which a placebo group is difficult to obtain. Hence, the design is particularly adapted to rare pediatric conditions. In this design, the subject is his/her own control, as in cross-over trials. However, a cross-over design would have involved the group of patients who receive sirolimus in the first phase to stop it in the second phase, even if it was beneficial. Moreover, cross-over design supposes that after the end of each treatment period, the disease returns to the initial state, which is perhaps not the case here, in that sirolimus might offer lasting improvement.

This randomized observational-phase trial also allows for maintaining sirolimus after the 12-month period of the trial if it is efficient. One of its potential drawbacks is premature termination of treatment. In case this happens, a final assessment (an MRI in our example) will have to be performed.

Because patients and care providers are not blinded to the treatment during that period, the primary outcome was chosen to be as objective as possible (i.e., changes in the volume of the VM seen on MRI). However, in practice, patients complain more about symptoms and complications linked to the VM, such as pain, oozing, bleeding, or functional impairment, than about the volume of the VM. Therefore, assessment of clinical efficacy and self-assessment on symptoms and complications are secondary outcomes of high importance. Safety data will be a focus in this pediatric phase 2 trial, because decisions for treatment in other children with VMs will be based on the benefit/risk ratio.

Hence, the main benefit of the study will be to resolve uncertainty concerning the efficacy and safety of sirolimus in children with slow-flow VMs, a subgroup of VAs that includes heterogeneous entities. If we demonstrate a benefit of sirolimus, the remaining question will be how long treatment has to be maintained.

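### Table 1 schedules adverse-event enquiry only after sirolimus starts, although its own footnote starts recording at consent, so the untreated months are not an equally ascertained comparator for safety

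*Protocol article*

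**What the plan says.** All references are to the protocol article.

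- **Secondary outcomes, Table 1.** The row for adverse and serious adverse events is marked in three columns: one month after the switch (calendar month 5 to 9), the on-sirolimus follow-up visits, and month 12. It is blank at screening, inclusion and switch. The table has no visit between inclusion and switch.
- **Footnote 6, attached to that row.** "adverse events will be recorded from when the informed consent form is signed".
- **Safety.** Events are self-declared in answer to open questions and coded later. Investigators also ask about them, "who will particularly check the most frequently AEs reported with sirolimus"; the effects named are stomatitis, digestive symptoms, asthenia, rash and mild infections. The text does not limit this questioning to one period.
- **Statistical methods.** "Regarding AEs, descriptive statistics (percentages) will be estimated". No period, denominator or exposure time is given.
- **Discussion.** "Safety data will be a focus in this pediatric phase 2 trial", because treatment decisions for other children will rest on the balance of benefit and risk.

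**The concern.** The duty to record begins at consent, but the schedule has nobody ask until about a month after the drug is started. Several of the prompted symptoms, such as mild infections, digestive upset, tiredness and rash, also occur in untreated children. If they are prompted only on treatment, they will look more frequent on treatment whether or not sirolimus causes them.

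The design rests on each child serving as his or her own control, and safety is part of the stated objective. The observational period is the natural background against which to read events on sirolimus. It can serve that purpose only if events in it are sought in a comparable way. This is a matter of data collection, so it cannot be put right at the analysis stage.

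**Working it through.** **1. The plan's own figures.** The document gives no adverse-event rate, so there is none to reproduce. The number carried into this check is the sample size: "We plan to recruit 50 patients". It agrees with its stated basis ("Considering a correlation of 0.5 between the outcomes assessed under the observational and sirolimus period"; "80% power to detect a 0.4 effect size, with a two-sided Type I error of 5"%). The SD of the paired difference is √(2 × (1 − 0.5)) = 1, and power is Φ(0.4 × √50 − 1.96) = 0.807, or 0.792 with the noncentral t.

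**2. Table and footnote side by side.**

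| Visit | Adverse-event row in Table 1 | Covered by footnote 6? |
|---|---|---|
| Inclusion | blank | yes, from consent |
| Between inclusion and switch (4 to 8 months) | no visit | yes |
| Switch | blank | yes |
| Switch + 1 month | marked | yes |
| On-sirolimus follow-up | marked | yes |
| Month 12 | marked | yes |

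The switch visit takes place in any case: physical examination, laboratory tests, MRI, photographs, self-assessment and quality of life are all marked there. The earliest scheduled enquiry about adverse events falls 5 to 9 months after inclusion, when the child has been on sirolimus for about a month.

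**3. Person-time.** The switch month is drawn uniformly, "considering five possible values (i.e., months 4, 5, 6, 7 and 8"), with 12 months of follow-up in all. Untreated time is 4, 5, 6, 7 or 8 months and sirolimus time is 8, 7, 6, 5 or 4 months; both average 6. With 50 children, equal allocation and complete follow-up, each period has 50 × 6 = 300 patient-months.

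**4. What unequal capture does when the drug has no effect.** Assume the same true rate in both periods, full capture when prompted, and a fraction c captured when not prompted. Neither the rate nor c is in the document. The apparent rate ratio is 1/c, whatever the rate. At 0.10 events per patient-month, 300 × 0.10 = 30 events are expected in each period:

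| c | Recorded untreated | Recorded on sirolimus | Apparent ratio |
|---|---|---|---|
| 25% | 7.5 | 30 | 4.0 |
| 50% | 15 | 30 | 2.0 |
| 75% | 22.5 | 30 | 1.3 |

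The same holds for percentages of children with at least one event, averaging 1 − exp(−h × t) over t = 4 to 8 months. With c = 50% the recorded untreated rate is h/2:

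| True rate h per month | Untreated, as recorded | On sirolimus, as recorded |
|---|---|---|
| 0.02 | 5.8% | 11.3% |
| 0.10 | 25.7% | 44.6% |
| 0.20 | 44.6% | 68.7% |

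**5. Does the varying exposure itself spoil the percentage?** At a constant hazard h, compare the pooled percentage with the risk at exactly 6 months:

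| h per month (assumed) | Pooled over 4 to 8 months | Fixed 6 months |
|---|---|---|
| 0.01 | 5.8% | 5.8% |
| 0.05 | 25.7% | 25.9% |
| 0.10 | 44.6% | 45.1% |
| 0.20 | 68.7% | 69.9% |
| 0.30 | 81.9% | 83.5% |

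The gap is at most about 1.5 points, so variable exposure is not the problem. Unequal enquiry is.

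**The case against.** The strongest reply is that footnote 6 governs the row. Recording runs from consent, the Safety section does not confine questioning to sirolimus, and the child is examined at the switch visit, so an investigator may well ask there. Laboratory safety also has values from before the drug, at inclusion and at the switch. All of this stands. A reader might infer that the trial has no safety comparator at all, and the document does not support that: some untreated-period data are to exist, and laboratory effects have a within-child baseline. But laboratory values say nothing about clinical symptoms, and a footnote that permits recording is not a scheduled question.

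A reader might also infer that, because exposure ranges from 4 to 8 months, a crude percentage has no stable meaning. Children at the two extremes do differ in risk, but no analysis in the protocol compares them. With blocked, uniform switch months the pooled percentage is close to a 6-month risk, as step 5 shows.

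Nor does the document say that every event on treatment will be attributed to sirolimus. The planned summary is descriptive and claims no attribution.

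Finally, exposure-adjusted rates and rate models are commonly left to an analysis plan, which is not shown here, so their absence is no fault. That too stands. It does not reach the visit schedule, which this document fixes, and fixes inconsistently.

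**Conclusion.** The point holds as a contradiction within Table 1 that has consequences for the safety objective. As scheduled, clinical events in the 4 to 8 untreated months depend on unsolicited report, whereas those on sirolimus are prompted at about one month and then every two months. The untreated period is therefore not an equally ascertained comparator, and the Statistical methods section does not say to which period its percentages refer.

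The size cannot be taken from the document. Under the assumptions in step 4, 25% to 75% unprompted capture gives a spurious rate ratio of 4.0 to 1.3. The figure rests on equal true rates, full capture when prompted, and investigators following the table as drawn. If sites already ask at the switch, the bias is smaller. The primary endpoint and its power are unaffected.

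**What to change.** 1. Reconcile the adverse-event row of Table 1 with footnote 6 by marking it at the switch visit. Ask the same open question and the same prompted items as on sirolimus, covering the time since inclusion, before the drug is started.
2. State in Statistical methods that adverse events are reported separately for the observational and sirolimus periods, with patient-months of exposure beside the percentages. Patient-months also cope with early stopping, which the Discussion foresees and which would upset the 300 to 300 balance.

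The cost is one block of questions at a visit that already takes place, and a few extra tables. The article reports a trial already recruiting, so the change helps only children who have not yet switched; for the others, the report should say how untreated-period events were collected.

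The downside is recall. One question spanning 4 to 8 months will miss mild events that shorter-interval enquiry on sirolimus would catch. The change narrows the ascertainment gap without closing it. Any difference between periods should be read descriptively, and as likely to overstate the drug effect for mild events.
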